## Abstract

**Introduction:**

Pakistan has a high burden of maternal, newborn and child morbidity and mortality. Several factors including weak scale-up of evidence-based interventions within the existing health system; lack of community awareness regarding health conditions; and poverty contribute to poor outcomes. Deaths and morbidity are largely preventable if a combination of community and facility-based interventions are rolled out at scale.

**Methods and analysis:**

Umeed-e-Nau (UeN) (New Hope) project aims is to improve maternal, newborn and child health (MNCH) in eight high-burden districts of Pakistan by scaling up of evidence-based interventions. The project will assess interventions focused on, first, improving the quality of MNCH care at primary level and secondary level. Second, interventions targeting demand generation such as community mobilisation, creating awareness of healthy practices and expanding coverage of outreach services will be evaluated. Third, we will also evaluate interventions targeting the improvement in quality of routine health information and promotion of use of the data for decision-making. Hypothesis of the project is that roll out of evidence-based interventions at scale will lead to at least 20% reduction in perinatal mortality and 30% decrease in diarrhoea and pneumonia case fatality in the target districts whereas two intervention groups will serve as internal controls. Monitoring and evaluation of the programme will be undertaken through conducting periodical population level surveys and quality of care assessments. Descriptive and multivariate analytical methods will be used for assessing the association between different factors, and difference in difference estimates will be used to assess the impact of the intervention on outcomes.

**Ethics and dissemination:**

The ethics approval was obtained from the Aga Khan University Ethics Review Committee. The findings of the project will be shared with relevant stakeholders and disseminated through open access peer-reviewed journal articles.

**Trial registration number:**

NCT04184544; Pre-results.

Strengths and limitations of this studyStrength of the Umeed-e-Nau project includes its quasi-experimental study design with district representative sample size.The household surveys will be powered to measure district level perinatal and child mortality estimates.Interventions to promote use of data for decision-making will be assessed in Pakistan for the first time.Potential limitations include challenges in accessing routine service delivery data for evaluation purposes.Challenges of working with or assessing role of lady health workers who are already overburdened with competing priorities.

## Introduction

Pakistan’s high maternal, neonatal and child mortality continues to hamper its overall growth and development.^1^ The global maternal mortality ratio in 2017 was estimated at 211 maternal deaths per 100 000 live births while 2019 estimates by United Nations inter-agency group for child mortality estimation (UN-IGME) estimate neonatal mortality rate at 18 deaths per 1000 live births and under-5 mortality rate is 39 per 1000 live births per year globally.^2 3^ Diarrhoea and pneumonia are two of the most common causes of child mortality; together, they account for more than 30% of all under-5 deaths in Pakistan.^4^

Several factors have contributed to the slow progress in maternal, newborn and child health (MNCH) in Pakistan, including social determinants such as poverty, high rates of illiteracy, lack of women’s and girls’ empowerment, voice, and high fertility rates. These are compounded by poorly functional health systems with low coverage rates of essential health interventions; wide disparities in geographic and socio-economic status, and a largely unregulated private sector providing poor quality health services^5^; and lack of community awareness and seeking timely care for health conditions.^6–8^ The majority of maternal, newborn and child deaths are preventable and treatable given the programmes are designed and delivered through an efficient public and private health system that takes into account the geographic and social structures.^9^

The health system and services operate through both public and private sectors in Pakistan. The public sector features a three-tiered health delivery system offering a range of essential public health interventions. The basic health units (BHUs) and rural health centres (RHCs) together with the community outreach programme that is, the Lady Health Worker (LHW) programme, provide core primary healthcare services; tehsil headquarter hospitals (THQs) and district headquarter hospitals (DHQs) serve as first level and second level referral facilities with ambulatory and inpatient care.^10^

An LHW is associated with the public health facility usually at the primary level and secondary level. Each LHW has a catchment population comprising of approximately 200 households.^11^ They target specific groups such as families with children under five and married couple eligible for family planning. Their key functions include increasing awareness about contraception, MNCH and nutrition. They also provide treatment for common illnesses like diarrhoea and acute respiratory infections (ARI), and distribute contraceptives for family planning. Furthermore, they identify danger signs for illnesses and refer people from the community to the health facility.

Around 70% of the population uses private providers, with expenses often paid out of pocket. Private providers are largely unregulated, though provincial governments have recently set up regulatory healthcare commissions to reduce high levels of unqualified providers and initiated licensing of private facilities.^1^

A number of strategies have been employed at community and facility levels to strengthen the public health service delivery system in Pakistan and elsewhere to improve the MNCH indicators.^12^ Such approaches have attempted to improve the quality of care through reviewing and updating training material^13^; conducting training and providing essential commodities to healthcare providers (HCPs) and community health workers (CHWs).^14^,^15^ For example, job aids-led intervention to improve quality of antenatal counselling in the Zou/Collines regions of Benin showed positive impact on danger sign recognition, birth preparedness, clean delivery and newborn care.^16^ Training of HCPs improved contact and quality across the continuum of care in Ghana.^17^ Furthermore, capacity building initiatives for healthcare workers have resulted in improved care quality of MNCH services in Jigawa State, northern Nigeria.^18^ Provision of job aids and training of LHWs in Gilgit region of Pakistan resulted in a significant reduction of 38% in perinatal mortality (PNM) rate.^19^ Furthermore, birth kits with 4% chlorhexidine for application to the umbilical cord were provided to traditional birth attendants to prevent omphalitis, thereby resulting in 38% reduction in neonatal mortality.^20^ A diarrhoea pack with oral rehydration salts (ORS) and amoxicillin was distributed. This was feasible and acceptable with an impact on the incidence of diarrhoea and reduced hospitalisation rates.^21^

Strategies to improve MNCH have also focussed on improving demand and supply side factors through community mobilisation activities and setting up of self-help groups. Formation of community groups in Magu district, Tanzania, to identify and resolve issues during pregnancy and childbirth resulted in an increased maternal health knowledge and positive behaviour changes among healthcare workers and community.^22^ A behaviour change intervention with women’s self-help groups was evaluated in rural India.^23^ They found significant improvement in using contraceptive methods, had institutional delivery, practiced skin-to-skin care, initiated timely breastfeeding, exclusively breastfed the child and provided age-appropriate immunisation. Furthermore, community mobilisation intervention led by LHWs in Hala, Pakistan, resulted in a 21% reduction in stillbirth rate and 15% neonatal mortality rate over a 2-year period.^24^ Community management of pneumonia through LHWs showed that they can successfully diagnose and treat severe pneumonia at home. The LHWs were able to effectively reach children with pneumonia where referral was difficult.^15^ Community case management of pneumonia through LHWs with oral amoxicillin at home was tested in two districts of Pakistan and proved to be safe and effective for treatment of severe pneumonia through LHWs.^25^

Furthermore, there is evidence on interventions for strengthening health information system.^26^For instance, a simple data improvement intervention led to completeness and accuracy of mother-to-child transmission of the HIV data in KwaZulu-Natal, South Africa.^27^

Finally, it is evident from previous studies that scaling up interventions using delivery platforms to reach poor and rural populations through community-based strategies and their successful implementation can prevent 58% of an estimated 367 900 deaths (15 900 maternal, 169 000 newborn and 183 000 child deaths) and 49% of an estimated 180 000 stillbirths in Pakistan alone.^15 19–21 24 26 28^

The UeN initiative aims to improve the health, well-being and survival of women and children in Pakistan through piloting and implementing effective MNCH interventions at scale in eight high-burden districts spanning three provinces and targeted to reach more than 11 million beneficiaries. The UeN initiative’s main goal is to scale up the evidence-based and cost-effective MNCH interventions within existing platforms at the community and facility level. Study goal, objectives and activities are detailed in figure 1. It is anticipated the UeN intervention scale-up in eight districts will reach approximately 1.7 million under-5 children, 1.5 million women of reproductive age and 8.6 million other civilians. The intervention will target 509 public health facilities (19 maternal and child health (CH) centres, 150 government dispensaries, 255 BHUs, 59 RHCs, 18 THQs, 6 DHQs and 2 civil hospitals), 500 private providers, 6518 LHWs and 300 CHWs. The primary hypothesis of the study is to assess whether roll out of proven and effective MNCH interventions at scale using existing public and private healthcare platforms at primary care level and secondary care level can reduce perinatal deaths by 20%, and diarrhoea and pneumonia case fatality rates by 30%.

**Figure 1 F1:**
[figure not shown]
Project design of Umeed-e-Nau. CHW, community health worker; HCP, healthcare providers; LHW, lady health worker; MIS, management information system; MNCH, maternal, newborn and child health; MNC&AH, Maternal, Newborn, Child and Adolescent Health.

### Objectives

Improve quality of MNCH care through development of training material and job aids for healthcare workforce; capacity building of healthcare workers; engaging private sector HCPs and ensuring supply of essential commodities at community and facility level.Improve access to and uptake of MNCH services through targeting supply and demand side factors. The focus will be to create awareness on healthy practices at household level; revitalising and creating village health committees; and expanding community-based services to areas, which are currently not covered.Promotion of the use of data for decision-making. Interventions will be used to improve data quality of public health facility and community level information systems. Furthermore, information system will be established for private HCPs.

This protocol paper will present the design and roll-out strategy for the UeN initiative. We will outline the setting, methods, implementation strategies, and monitoring and evaluation processes of the project roll-out spanning years 2017 to 2022 (project timeline shown in figure 2).

**Figure 2 F2:**
[figure not shown]
Umeed-e-Nau project timeline. LHW, lady health worker; M&E, Monitoring and Evaluation.

## Methods and analysis

### Study setting

Covering three provinces in the country, the UeN scale-up component will be implemented in eight districts (location of interventions by theme is shown in figure 3). Study districts were selected to be predominantly rural, and had some of the highest MNCH morbidity and mortality outcomes in the country. An important consideration was also ensuring that the selected districts did not have other major public health campaigns to avoid conflation or dilution of UeN impact. High-burden districts were strategically selected to demonstrate effective change models in difficult geographies so as to maximise project impact on population outcomes. Table 1^29^ outlines relevant demographic, health and contextual indicators for each study district.

**Table 1 T1:** Distribution of demographic and health indicators for maternal, newborn and child health indicators in districts selected for programme implementation in UeN initiative in Pakistan

	Maternal and newborn health		Maternal health	Newborn health	Child health			
	Lasbela	Badin	Sanghar	Nasirabad	Qambar Shahdadkot	Muzaffargarh	Jafferabad	Rahim Yar Khan
Population	574 292	1 804 516	2 057 057	490 538	1 341 042	4 325 483	513 813	4 814 006
Under-5 population	74 657	202 106	230 390	13 837	150 197	462 756	14 191	625,8208
HDI	0.416	0.412	0.491	0.311	0.456	0.584	0.345	0.625
HDI rank	85	87	72	98	77	58	94	51
Tehsils/talukas	5	5	6	4	7	4	3	4
Union councils	22	12	63	31	52	93	38	139
Vaccination coverage—Children 12 to 23 months (fully immunised)	28.8	45.5	47.4	28.8	25.6	82.1	28.8	72.0
Antenatal care during last pregnancy (%)	55.9	83.1	56.8	55.9	64.5	37.4	55.9	30.8
Facility births (%)	34.6	64.8	40.0	34.6	48.7	50.7	34.6	62.0
Delivery by skilled birth attendant	38.2	66.6	42.1	38.2	49.7	52.7	38.2	65.6
Postnatal consultation in health facility	29	75.0	61.6	29	68.2	56.9	29	63.9
Access to tap water	29.6	20.7	20.7	28.6	5.8	6.5	28.6	21.4
Access to toilet (flush)	17.6	70	51.8	16.5	77.3	72	16.5	60.5
Number of LHWs	153	1010	883	309	680	1891	130	1723
LHWs coverage %	50	80	66	60	59	51	50	80
Number of hospitals	125	145	116	97	271	248	97	260
Number of RHCs	4	12	5	1	4	12	1	19
Number of BHUs	42	36	58	19	4	76	19	103

BHU, basic health units; HDI, human development index; LHW, lady health worker; RHC, rural health centres; UeN, Umeed-e-Nau.

**Figure 3 F3:**
[figure not shown]
Map showing the geographic location of the programme districts in three provinces of Pakistan. GB, Gilgit-Baltistan; KPK, Khyber Pakhtunkhwa; PATA, Provincially Administered Tribal Areas.

### Study design

In order to evaluate the impact of scaling up MNCH interventions, a quasi-experimental study design will be used. Each of the eight districts will be treated as an intervention site, and will be grouped together broadly into two areas to span MNCH interventions (figure 3). As detailed below, group 1 will receive maternal and newborn health (MNH) interventions, while group 2 will receive CH interventions. Each group will serve as the ‘control’ for the other. This design will help us evaluate independent and combined effect of MNCH interventions to address MNCH outcomes.

Site allocation to group 1 and 2 were done through extensive consultation with provincial government, bilateral donors and UN agencies, and UeN project team. Factors that were considered during intervention allocation included level of MNCH morbidity and mortality, assuring geographical diversity across the provinces, varying size of the districts and government MNCH priorities in those districts (so that those areas that were focused on improving CH, for example, received the CH interventions). This design might have ethical implications such as not providing all MNCH related evidence-based interventions to the entire population; however, population in control areas will continue to receive all the routine services which are part of the public sector standard of care and some additional MNCH intervention as per allocation to the type of intervention group. Furthermore, this ethical concern has been addressed by developing partnerships with Government, development agencies and private providers who have agreed to include UeN interventions in the existing health system, if the evidence generated suggests their effectiveness and feasibility when delivered at scale.

### Sample size

The sample size for the household surveys will be calculated using the assumption that that the roll out of proven and effective interventions within existing health delivery platforms for MNCH will lead to significant reduction in PNM rate (20% compared with baseline) and at least 30% reduction in diarrhoea and pneumonia case fatality rates in the target districts for the proposed UeN scale-up initiative. PNM will be used as the primary outcome for all sample size projections. A stratified two-stage cluster sampling approach will be used to calculate sample size. Moreover, it is important to power the study to provide a detectable difference between the maternal and newborn health group, and the CH group. We will use a before and after design for sample size calculation. For MNH districts, assuming a 20% reduction in the PNM from the baseline PNM of 75 per 1000 live births (Pakistan Demographic Health Survey 2012 to 2013 for rural Pakistan)^30^ with a power of 80% to detect the difference in the PNM between baseline, and the endline household survey, a type I error of 5%, design effect of 1.515 and an annual attrition of 10% per year, at least 19 582 households will be enrolled in the survey. For CH intervention districts, assuming a 30% reduction in the post neonatal death (PND) rate of 19/1000 live births at baseline (Pakistan Demographic Health Survey 2012 to 2013 for rural Pakistan) with a power of 80% to detect the difference in the PND between baseline and the endline household survey, a type I error of 5%, design effect of 1.388 and an annual attrition of 10% per year, at least 19 210 households have to be enrolled in the survey.

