### Study outcome measures

The primary outcomes of interest are reduction in PNM rate (20% compared with baseline) and at least 30% reduction in diarrhoea and pneumonia case fatality rates. The secondary outcomes include coverage of essential intervention across the continuum of care and maternal, newborn and child morbidity rates (table 2).

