#### Statistical analysis

Basic frequencies will be calculated for demographic, social equity, primary outcome and secondary outcome of the study at baseline, and midline surveys and endline surveys. Furthermore, the baseline data will be analysed using multivariate analytical methods to assess the perinatal and child mortality estimates and its determinants.

The overall impact of the UeN project will be measured assuming parallel trends within the two MNH and CH groups, in the absence of any intervention, difference-in-difference estimates will be used to assess the impact of the intervention on outcomes. An interaction term between group (intervention/control) and survey wave (baseline/end-line) will be included in each model. All the analyses will be done using Stata.

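### The 80% power applies to within-group change, not to the group-by-wave interaction that measures impact, for which it would be about 50% on like assumptions

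*Protocol article*

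**What the plan says.** The Sample size section sets a between-group aim: "it is important to power the study to provide a detectable difference between the maternal and newborn health group, and the CH group". The next sentence reads "We will use a before and after design for sample size calculation". The MNH districts are sized "assuming a 20% reduction in the PNM from the baseline PNM of 75 per 1000 live births", with design effect 1.515, giving at least 19 582 households. The CH districts are sized "assuming a 30% reduction in the post neonatal death (PND) rate of 19/1000 live births at baseline", with design effect 1.388, giving at least 19 210. In both cases the 80% power and 5% type I error are tied to baseline versus endline in that group.

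The Study design section states "Each group will serve as the ‘control’ for the other". The Statistical analysis section says that, assuming parallel trends, "difference-in-difference estimates will be used to assess the impact of the intervention on outcomes", and adds: "An interaction term between group (intervention/control) and survey wave (baseline/end-line) will be included in each model".

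The Study outcome measures section words the target as change from own baseline: "The primary outcomes of interest are reduction in PNM rate (20% compared with baseline". No power or detectable effect is given for the interaction.

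**The concern.** A before/after test compares two survey cells. A difference-in-difference compares four, and the two control cells add sampling variance. A sample that gives 80% power for the first gives less for the second unless the control group is very large. The section states a between-group aim and then uses a calculation that does not address it.

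A null interaction could therefore be read as failure of a programme with 80% power, when the chance of detecting the planned effect was nearer one half. Conversely, a fall from own baseline includes any background decline, so progress towards the 20% target is not by itself evidence of a controlled effect.

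**Working it through.** **Inputs (Sample size section).** PNM 0.075 to 0.060, difference 0.015. PND 0.019 to 0.0133, difference 0.0057. Power 80%, type I error 5% (two-sided assumed; the article does not say). Design effects 1.515 and 1.388.

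**1. The plan's own figures.** A standard two-proportion formula with pooled variance gives 4 391 (PNM) and 7 676 (PND) births per wave. With design effects these become 6 652 and 10 654, or 13 305 and 21 309 over two waves. I found no single recipe that yields both household totals. A continuity correction, two waves and division by 0.7 give 19 578 for MNH (stated 19 582), but about 31 800 for CH (stated 19 210). Births per household, waves covered and years of attrition are not given. The check below therefore takes the stated 80% as true and works back to effective births, n, per group and wave.

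**2. Births giving 80% before/after power.** n = (1.960 + 0.842)² × (p1q1 + p2q2) / d², with unpooled variance.
- PNM: 7.849 × (0.069375 + 0.056400) / 0.015² = 4 388
- PND: 7.849 × (0.018639 + 0.013123) / 0.0057² = 7 673

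**3. Interaction power, absolute scale.** The control has the same baseline rate, no change and the same n. SE² = (3·p1q1 + p2q2) / n; power = Φ(d/SE − 1.960).
- PNM: SE = √(0.264525 / 4 388) = 0.00776; z = 1.93; power 49%
- PND: SE = √(0.069040 / 7 673) = 0.00300; z = 1.90; power 48%

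The variance is 2.10 and 2.17 times that of the before/after contrast.

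**4. Interaction power, log scale.** SE² = [3(1−p1)/p1 + (1−p2)/p2] / n.
- PNM: SE = √(52.667 / 4 388) = 0.1096; z = 0.2231 / 0.1096 = 2.04; power 53%
- PND: SE = √(229.08 / 7 673) = 0.1728; z = 0.3567 / 0.1728 = 2.06; power 54%

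**5. Effect detectable with 80% interaction power.** Solve effect/SE = 2.80, with the endline rate moving with the effect.

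| | Planned | Absolute scale | Log scale |
|---|---|---|---|
| PNM | 20% | 28.7% | 26.8% |
| PND | 30% | 43.4% | 39.1% |

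**6. Sensitivity (absolute scale; PNM, PND).**
- Control size equal to the other group's computed effective births: 59%, 36%.
- Flat control four times as large: 70%, 69%.
- A 10% background fall in both groups with the planned effect on top: 43%, 42%.
- Control falls 10% while the group's own total fall stays at 20% or 30%: 16%, 25%.
- Both tests one-sided, sized accordingly: about 53%, 52%.

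**The case against.** The 80% is correctly labelled in the article as a baseline-to-endline figure. A reader might infer that the study's power is really 50%, but the documents do not support so flat a statement. The 50% depends on the stated 80% being true and on an equal, flat control. If every household gave one birth in each wave with no loss, effective births would be 19 582/1.515 = 12 925 and 19 210/1.388 = 13 840, and interaction power would be 91% (PNM) and 72% (PND). Before/after power would then be 99.8% and 96%, so the stated 80% would not hold either. This objection limits the size of the point. It leaves the mismatch in place.

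A reader might also infer that background decline alone could meet the PNM target. The documents give no rate. At an assumed 2–4% a year, five years give 10–18%, below 20%. Decline contributes to the target but does not reach it on that assumption, and the plan already assigns impact to the controlled estimate.

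Nor does the PND result give power for the CH primary outcomes. Table 2 lists diarrhoea and pneumonia case fatality and does not list PND, which serves only for sizing.

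Pooling midline with endline is no safe rescue. If the full effect is present by midline, power is about 60% (PNM) and 58% (PND). If only half is present, it is about 38% and 36%, worse than endline alone.

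**Conclusion.** The point holds in conditional form. The sizing, the stated between-group aim and the impact estimator do not fit together, and nothing in the article reconciles them. The size given in steps 3 to 5 rests on three assumptions: before/after power of 80%, a control of equal effective size, and no change in that control. Under a flat control the direction is firm, since the control cells only add variance and interaction power stays below before/after power for any finite control. Between-district variation in change, with four districts per group, is not in these figures and would lower power further. The actual power of the planned households remains unknown.

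**What to change.** In Sample size, label the 80% as applying only to the within-group change. Add the power or detectable effect of the group-by-wave interaction at the fixed sample, with the assumed control-group size and trend, births per household, waves covered and years of attrition. Give it on the scale of the model to be used, since the detectable effects differ between scales. State that PND is a sizing outcome only, and that no interaction power for the case-fatality outcomes follows from it.

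In Study outcome measures, judge the PNM target by the difference-in-difference effect and not by change from own baseline alone, because background decline contributes to the latter.

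The cost is wording in two sections and no extra households. The stated power becomes less favourable. Keeping 80% for the planned effects instead would take about 9 228 (PNM) and 16 679 (PND) effective births per group and wave, 2.10 and 2.17 times the before/after number.

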**Household surveys**

Household surveys will be conducted at three time points, baseline, at approximate mid-line when the interventions have been implemented at scale for at least 18 to 24 months, and at the end of the project (towards the end of year 5). The surveys will collect information to assess the impact of the interventions on primary outcome and secondary outcome indicators (listed in table 2).

**Table 2 T2:** List of primary and secondary outcomes

Outcomes	Definition
Primary outcomes	
Perinatal mortality rate	The number of stillbirths and deaths in the first week of life per 1000 total births
Diarrhoea case fatality	Per cent deaths among under-5 children due to diarrhoea
Pneumonia case fatality	Per cent deaths among under-5 children due to pneumonia
Secondary outcomes	
Maternal and newborn health	
Contraceptive use	Per cent of mothers aged 15 to 49 who are using modern contraceptive method
Antenatal care coverage	Per cent of mothers aged 15 to 49 who received antenatal care ≥4 times during pregnancy with their youngest living child aged <6 months
Tetanus toxoid coverage	Per cent of mothers aged 15 to 49 who received ≥2 doses of tetanus toxoid during pregnancy with their youngest living child
Skilled birth attendant at time of delivery	Per cent of mothers aged 15 to 49 whose youngest living child was delivered by skilled health personnel
Institutional delivery	Per cent of mothers aged 15 to 49 whose youngest living child was delivered in a health facility
Postnatal care coverage	Per cent of mothers aged 15 to 49 who received postnatal care (for self or for infant) within 3 days of birth
Early initiation of breastfeeding	Per cent of mothers aged 15 to 49 whose youngest living child was breastfed within 1 hour of birth
Exclusive breastfeeding	Per cent of mothers aged 15 to 49 whose youngest living child was exclusively breastfed
Vaccination coverage among under-5 children	Per cent of mothers aged 15 to 49 whose youngest living child received ≥3 doses of diphtheria, pertussis and tetanus/pentavalent vaccine when aged 12 to 23 months
	Per cent of mothers aged 15 to 49 whose youngest living child received ≥1 dose of measles vaccine when aged 12 to 23 months
	Per cent of mothers aged 15 to 49 whose youngest living child was fully immunised
Care-seeking for diarrhoea among under-5 children	Per cent of mothers aged 15 to 49 whose youngest living child with diarrhoea in the previous 2 weeks received oral rehydration salts and zinc

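### The child-health districts are sized on a 30% fall in post-neonatal mortality, which is not a listed outcome, so the stated 80% power is not shown to apply to the diarrhoea and pneumonia case-fatality outcomes

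*Protocol article*

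**What the plan says.** All references are to the protocol article.

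- **Hypothesis and outcomes.** The Abstract, the end of the Introduction and Study outcome measures all set a 30% fall in diarrhoea and pneumonia case fatality. Table 2 lists the two diseases as separate primary outcomes in under-5 children; the pneumonia entry is defined as "Per cent deaths among under-5 children due to pneumonia".
- **Basis of sizing.** The Sample size section opens with the same 30% assumption for case fatality and then states: "PNM will be used as the primary outcome for all sample size projections".
- **CH calculation.** Later the paragraph turns to a different rate: "For CH intervention districts, assuming a 30% reduction in the post neonatal death (PND) rate of 19/1000 live births at baseline". It ties the power to that same rate, in these words: "with a power of 80% to detect the difference in the PND between baseline and the endline household survey". The remaining inputs are 5% for the type I error, 1.388 for the design effect and 10% yearly attrition, and the result is a minimum of 19,210 households. The rate is not restricted by cause.
- **Status of PND.** It is neither a primary nor a secondary outcome in Table 2. Child mortality appears elsewhere only as something the surveys will estimate (Strengths and limitations; Statistical analysis).
- **Cause share.** The only figure is in the Introduction, which says of diarrhoea and pneumonia: "together, they account for more than 30% of all under-5 deaths in Pakistan".

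**The concern.** There are two faults on the face of the text. First, the section says one endpoint (PNM) serves all projections and then uses another (PND) for four of the eight districts. Second, the 30% hypothesised for fatality from two diseases has been moved, without a stated link, to a death rate covering every post-neonatal cause.

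The age bands differ as well: PND is a post-neonatal rate per live births, while the Table 2 outcomes concern under-5 children.

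At stake is how the result will be read. A reader will take 80% power as covering the CH primary outcomes, and could then read a non-significant CH result as stronger evidence against the programme than the stated design supports.

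**Working it through.** **Inputs from the Sample size section.** PND falls from 19 to 19 × 0.7 = 13.3 per 1000 live births; power 80%; type I error 5%; design effect 1.388; attrition 10% a year; 19,210 households; before/after comparison. Assumed, because not stated: a two-sided test and equal numbers in the two surveys.

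**Step 1. The plan's own figure.** For two proportions,

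n = [1.96·√(2p̄(1−p̄)) + 0.842·√(p₁(1−p₁) + p₂(1−p₂))]² / (p₁−p₂)²

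With p₁ = 0.019, p₂ = 0.0133 and p̄ = 0.01615, n = 7,676 births per survey. Multiplying by 1.388 gives 10,654.

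With a continuity correction, n = 8,023; × 1.388 = 11,136; ÷ 0.9⁵ (five years of attrition, assumed) = 18,859, which is 1.8% below 19,210. The match is weak. Years of attrition, sidedness and births per household are not given, some one-sided variants also come close, and the same rule gives about 11,604 for the maternal and newborn districts against 19,582 stated. The point does not depend on this match, because the choice of endpoint and effect is at issue and not the arithmetic.

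**Step 2. From case fatality to PND.** Let s be the share of post-neonatal deaths due to the two diseases. With incidence and all other causes unchanged, a 30% fall in their fatality gives

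relative fall in PND = 30% × s

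This equals 30% only if s = 100%. At s = 50% the two diseases' deaths would have to fall by 60% to produce the assumed PND reduction; at s = 30% they would have to disappear.

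**Step 3. Illustrative power for PND under the hypothesised effect.** The document gives no s for post-neonatal deaths, so a range is assumed. Two sample sizes are shown: 10,654 births per survey (7,676 after the design effect), and the generous case in which all 19,210 households give one birth in each survey with no attrition (19,210 ÷ 1.388 = 13,840 after the design effect).

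| s (assumed) | Fall in PND | PND after, per 1000 | Power, 10,654 births | Power, 19,210 births | Births needed for 80%, relative to 10,654 |
|---|---|---|---|---|---|
| 30% | 9% | 17.29 | 12% | 19% | 12.5 times |
| 50% | 15% | 16.15 | 27% | 44% | 4.3 times |
| 60% | 18% | 15.58 | 37% | 59% | 3.0 times |
| 70% | 21% | 15.01 | 48% | 73% | 2.1 times |
| 100% | 30% | 13.30 | 80% | 96% | 1.0 |

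**Step 4. The Table 2 outcomes themselves.** Their power cannot be computed, because no baseline case fatality is given. A nearby quantity, the combined death rate from the two diseases per live birth (19 × s per 1000, falling 30%), has power of 33%, 51%, 58% and 65% for s = 30%, 50%, 60% and 70% at 10,654 births, and 54%, 75%, 83% and 88% at 19,210 births. That is not the outcome Table 2 defines.

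**The case against.** The strongest reply accepts the mismatch and challenges its size.

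- **The share is not documented.** The Introduction's figure is a floor, and it covers all under-5 deaths, neonatal ones included. The post-neonatal share may be well above 30%. This stands, so the 12% should not be read as the expected value.
- **Incidence may fall too.** The CH package follows the pneumonia and diarrhoea action plan, the Figure 4 legend lists water, sanitation and hygiene education, and the dissemination section speaks of reducing incidence of both diseases. If incidence fell by 20% (assumed), deaths would fall by 1 − 0.8 × 0.7 = 44%, and PND power at 10,654 births would be 52%, 68% and 82% for s = 50%, 60% and 70%. This also stands as a limit on the figures. It does not rescue the plan, which neither states nor quantifies such an effect.
- **The number of births is inferred.** The plan counts households. On the generous count, the combined cause-specific rate reaches 83% at s = 60%.

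A reader might therefore infer that the CH arm has been shown to lack 80% power, or that a null result would tell nothing. The documents support neither. Power depends on quantities they do not give, and a confidence interval for PND would still be informative. Nor should power for a cause-specific death rate per live birth be presented as power for the Table 2 outcomes.

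**Conclusion.** The point holds as a mismatch of endpoint and effect. Two parts need no assumption: the Sample size section contradicts itself on PNM and PND, and the CH power belongs to an endpoint missing from Table 2. A third follows from the dilution formula: with incidence and other causes unchanged, a 30% fall in case fatality yields a 30% fall in PND only if the two diseases cause every post-neonatal death, which the protocol does not claim. So the 80% is not shown to apply to the CH primary outcomes; it has not been proved out of reach for every cause-specific endpoint.

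Over s = 30% to 70%, illustrative PND power is 12% to 48% at 10,654 births per survey and 19% to 73% at 19,210. These ranges rest on the assumed share, unchanged incidence, the inferred number of births and a two-sided before/after test.

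**What to change.** In the Sample size section:

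1. Limit the sentence naming PNM as the basis of all projections to the maternal and newborn districts.
2. State that the CH sample of 19,210 households has 80% power only for a 30% before/after fall in all-cause PND, and that this does not carry over to the two case-fatality outcomes.
3. Report power for the hypothesised cause-specific effect as a range, with the assumed cause share, incidence effect and births per household written beside it.

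In Table 2, add all-cause post-neonatal mortality as the outcome for which the CH survey is sized. Keep diarrhoea and pneumonia case fatality as primary outcomes, with no claim of power attached; the hypothesis in the Abstract, Introduction and Study outcome measures can then stand.

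The cost is wording in one paragraph and one added row. No extra households are needed, but the stated power will look less favourable.
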